### Assessment Procedures

Researchers 'blinded' to the subject's group allocation will perform all followup assessments. Each subject will undergo the following procedures at baseline assessment and again at 12 and 24 weeks. Subjects will be required to attend 3 assessment visits within a 2 week period, with each visit separated by at least 24 hours.

#### Visit 1

Subjects will undergo:

(i) Two unencouraged 6-minute walk tests (separated by a rest period of at least 30 minutes) that include monitoring of HR via telemetry (Polar FS3C heart rate monitor, Sportstek, Victoria, Australia), oxygen saturation (SpO_2_) (Respironics 512 pulse oximeter and finger sensor, Philips, Massachusetts, United States) and assessment of symptoms (Borg CR10 [31] dyspnoea and rating of perceived exertion [RPE]).

(ii) Familiarisation with the cycle ergometer and gas analysis equipment.

(iii) HRQoL assessment using the CAMPHOR [32], which has been recently validated in the Australian PAH population [33], and the Medical Outcomes Study Short Form 36 (SF36) Version 2 [34].

(iv) Assessment of physical activity using the International Physical Activity Questionnaire [35].

#### Visit 2

An incremental cardiopulmonary exercise test (CPET) using a continuous ramp protocol (Lode Corival cycle ergometer, Lode, Groningen, Netherlands) [36], to volitional exhaustion with breath by breath gas exchange analysis (Medical Graphics CPX-D, Medgraphics, Minnesota, United States) will be carried out. The test protocol will comprise 3 minutes of upright rest on the bicycle, followed by 3 minutes of unloaded pedalling (0 W). Subsequent workloads will be increased by 5 W/min, 10 W/min or 15 W/min increments depending on the subject's age, gender, weight, 6MWD and diffusing capacity of the lung for carbon monoxide (DLCO) [30]. The aim will be to achieve a test duration of 8 to 12 minutes from commencement of the incremental phase of the test to peak exercise due to volitional task cessation or symptom limitation. Standard criteria will be used to determine if test termination is required for safety reasons [36].

#### Visit 3

A constant workload exercise test will be performed using the same system used for the incremental CPET. The test protocol will comprise 3 minutes of upright rest on the bicycle, followed by 3 minutes of unloaded pedalling (0 W), followed by a step increase in workload to 75% of the peak workload achieved during the incremental CPET. Subjects will be instructed to cycle until voluntary task failure, aiming for a test duration of 6 to 8 minutes. The test will be terminated after 20 minutes of loaded cycling if volitional exhaustion is not reached. Standard criteria will be used to determine if test termination is required for safety reasons [36]. Constant workload cycle tests, at 12 and 24 weeks, will be performed using the identical workload to that used at the baseline assessment.

### Exercise group

Subjects will attend a 12 week, outpatient, individualised, supervised exercise training program involving 3 exercise classes (one hour duration) each week. The sessions will focus on lower limb endurance training (walking and cycling). Lower limb functional strength training (step ups and sit to stands) and endurance training of the upper limbs will also be included with the aim of improving the subject's ability to undertake activities of daily living. Heart rate will be monitored continuously via telemetry (Polar FS3C heart rate monitor, Sportstek, Victoria, Australia) and SpO_2 _(Respironics 512 pulse oximeter and finger sensor, Philips, Massachusetts, United States) prior to and following each exercise. Intensity for the lower limb endurance exercises will be prescribed with the aim of achieving 60-70% HR max (based on age predicted maximum, 220-age [37]), while maintaining SpO_2 _≥ 92% and symptom intensity (Borg CR10 dyspnoea < 4 and RPE < 4). Exercise intensity will be progressed, based on the individual's response to training to maintain HR within the target HR range. The lower limb functional strength training and upper limb endurance exercises will be performed at an intensity that elicits subjective reports of muscle fatigue (RPE 3 to 4) following the completion of 2 sets of 10 repetitions.

#### Home exercise program

The subjects randomised to the exercise group will be asked to commence one session per week of their home exercise program during the last 4 weeks of their supervised program. This is to ensure subjects have the opportunity to discuss the program with the supervising physiotherapist who can assist in troubleshooting any problems that may arise. On completion of the supervised program, subjects will increase the frequency of their home program to 3 sessions per week for an additional 12 weeks. The home program will comprise lower limb endurance training (walking) and lower limb functional strength exercises (step ups and sit to stands). Subjects will be required to record each session on an exercise log. The program will be individually tailored based on the individual's performance during the supervised exercise classes. To guide the home exercise training intensity, symptoms during the supervised period will be correlated to a HR maximum of 120 bpm [15]. Subjects will aim to achieve these symptom responses (Borg CR10 dyspnoea < 4 and RPE < 4) at home to guide exercise intensity.

### Withdrawal Criteria

Subjects will be withdrawn from the study if they demonstrate deterioration in their clinical status (time to clinical worsening), defined by the presence of two or more of the following [38,39]: (i) escalation of medical therapy (increased dose of medication or commencement of intravenous epoprostenol); (ii) deterioration (≥ 1) in WHO functional class; (iii) development of right heart failure (as indicated by increased jugular venous pressure, new/worsening hepatomegaly, ascites or peripheral oedema); (iv) resting echocardiogram changes (deterioration in right ventricular size and function, right atrial size, pulmonary arterial systolic pressure (PASP) and, where PASP cannot be determined, pulmonary acceleration time); (v) oedema that does not respond to oral diuretics; (vi) hospitalisation for PAH; (vii) listing for transplantation; (viii) ≥ 20% deterioration in 6MWD (ix) progressive worsening of dyspnoea at rest or on exertion over the past 3-5 days [40]; (x) deterioration in ventilatory efficiency (V_E_/VCO_2_) reflecting worsening gas exchange.

Subjects may also be withdrawn from the study at their request or if they experience a serious adverse event during or up to 24 hours following an exercise training session and it is deemed unsafe to continue participation by the treating medical officer from the Royal Perth Hospital Pulmonary Hypertension Service. Adverse events comprise: (i) an incident requiring a medical emergency team call (according to Royal Perth Hospital criteria); (ii) exercise-related incident requiring presentation to the Emergency Department or General Practitioner; (iii) hospital admission due to PAH or worsening right heart failure; (iv) an incident resulting in the patient ceasing exercise during class (chest pain, syncope, worsening dyspnoea despite rests, hypotension/hypertension, bradycardia/tachycardia (as measured by a polar monitor and confirmed by palpation), nausea (associated with sweating, pallor and/or tremor), vagueness, vasovagal, arrhythmia); (v) death.

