(ii) Exercise training is safe and improvements in exercise capacity will be achieved without evidence of clinical worsening

(iii) An additional 12 week home exercise program will maintain or further improve the benefits gained during the 12 week, supervised, outpatient program.

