### Outcomes

The primary outcomes of this study will be:

(i) Peak VO_2_;

(ii) Anaerobic threshold;

(iii) Endurance time measured from the constant workload cycle ergometry test;

(iv) HRQoL measured using the CAMPHOR and SF 36 Version 2;

(v) The number of reported acute adverse events (i) reported during exercise training and (ii) resulting in the withdrawal of a subject from the study.

The secondary outcomes of this study will be:

(i) Ventilatory variables at isotime during the constant workload cycle ergometry test (ventilatory equivalent for carbon dioxide [VE/VCO_2_] and end tidal carbon dioxide [PetCO_2_] to describe gas exchange);

(ii) Change in WHO functional class;

(iii) 6MWD (measured from the best of two 6MWTs at each assessment);

(iv) Worsening clinical status (see withdrawal criteria).

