### Statistical methods

Data will be analysed using SPSS software (Version 17.0; SPSS Inc; Chi). Data that are not normally distributed will be transformed and if transformation fails to satisfy normality, non-parametric tests will be used. The primary and secondary outcomes in the exercise and control groups will be compared using two-way analysis of variance to account for group and time interactions. Statistical relationships between outcome variables will be analysed using Pearson's or Spearman's correlations as appropriate. Data will be analysed using (i) per protocol analysis and (ii) intention-to-treat analysis. Per protocol analysis will be restricted to the data from subjects who complete all assessments and for the exercise group who attend at least 75% of their exercise classes. The required number of sessions must be achieved within a period of 15 weeks for both the supervised and home exercise training programs, allowing for intercurrent illness and other factors that may impact on an individual's ability to attend sessions. The last-observation-carried-forward method will be used to impute missing data at 12 and 24 weeks for the intention-to-treat analysis [41]. The Berger-Exner [42] test will be carried out to determine whether selection bias has been introduced into the study.

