## Discussion

This study will be the first randomised controlled trial to evaluate the physiological, clinical and psychological changes that occur following outpatient-based, whole body exercise training in PAH. We hypothesise that exercise training will improve exercise capacity and HRQoL. Adverse events and clinical worsening will be monitored in order to address theoretical safety concerns regarding the potential deleterious effects exercise may have on the pulmonary vasculature and right heart function. Assessment of the subjects following 12 weeks of home exercise program will determine whether the subjects were able to safely maintain the benefits achieved during the supervised exercise training period. Furthermore, this study will contribute to clinical practice guidelines, which will have important implications for the future management of patients with PAH.

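### Secondary outcome (iv), worsening clinical status, borrows a two-of-ten withdrawal rule that omits death, so a death without two documented items is scored as no worsening

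*Protocol article*

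**What the plan says.** The Outcomes section gives secondary outcome (iv) as "Worsening clinical status (see withdrawal criteria" and adds nothing further. The definition is therefore the one under Withdrawal Criteria: deterioration is "defined by the presence of two or more of the following", and ten items follow. They are therapy escalation, a worse WHO class, right heart failure, echocardiographic change, diuretic-resistant oedema, PAH admission, transplant listing, a 20% or greater fall in six-minute walk distance (6MWD), progressive dyspnoea, and poorer VE/VCO2. PAH admission and transplant listing ("vi) hospitalisation for PAH; (vii) listing for transplantation") carry one item's weight each, like the rest. Death is not among the ten.

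Death appears in a separate list of adverse events in the same section, as does admission for PAH or worsening right heart failure. Adverse events enter the outcomes through primary outcome (v), the number of acute events "reported during exercise training and (ii) resulting in the withdrawal of a subject from the study".

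Hypothesis (ii) in the Background says that training is safe and that "improvements in exercise capacity will be achieved without evidence of clinical worsening". The Discussion states: "Adverse events and clinical worsening will be monitored in order to address theoretical safety concerns".

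**The concern.** A withdrawal rule and an outcome serve different purposes. A rule for taking living subjects out of a trial has no need to mention death, and asking for two signs protects against reacting to a single soft one. When the same list becomes an outcome, leaving out death means that the worst result does not register.

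This matters because the Background gives the perceived risk of sudden cardiac death as a reason why exercise was discouraged in PAH. A sudden death is also the kind least likely to be preceded by two documented items. Of the two things the Discussion says will be monitored for safety, clinical worsening is the one defined without reference to training sessions, so it is the natural event comparison between arms. As defined, that comparison could agree with hypothesis (ii) despite a death in the exercise arm.

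**Working it through.** The plan states no figure for this outcome, so there is none to reproduce. The check has three parts.

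**1. The rule applied to cases.** Inputs: the ten items and the two-item threshold under Withdrawal Criteria. A subject is scored as worsened if at least two of the ten are present.

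| Case | Listed items present | Scored as worsened? |
|---|---|---|
| Death alone | 0 | No |
| PAH admission, then death | 1 | No |
| Transplant listing, then death | 1 | No |
| PAH admission alone | 1 | No |
| Transplant listing alone | 1 | No |
| PAH admission and therapy escalation | 2 | Yes |
| 20% fall in 6MWD and poorer VE/VCO2 | 2 | Yes |

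A death that follows a documented decline with two items would count, because of those items. The deaths missed are those with none or one on record. 6MWD and VE/VCO2 come from tests scheduled at baseline, 12 and 24 weeks, so a subject who dies between visits may never supply them.

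**2. Whether primary outcome (v) fills the gap.** Its first limb is acute events during exercise training. Controls do not train, so it cannot count a control death. Its second limb is events resulting in withdrawal. The adverse-event route to withdrawal under Withdrawal Criteria is tied to a serious event during a training session or in the 24 hours after it. A control death, or an exercise-arm death away from sessions, fits neither limb clearly.

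**3. What one event weighs.** Input: 17 per arm (Sample size calculation). The occurrence of one event is an assumption, for illustration only.

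- One event: 1/17 = 5.9%.
- Exact (Clopper-Pearson) 95% upper limit for 0/17: 1 − 0.025^(1/17) = 19.5%. For 1/17 it is the p that solves (1 − p)^17 + 17p(1 − p)^16 = 0.025, which is 28.7%.
- Difference, exercise minus control, Newcombe 95% limits. With the event counted, 1/17 − 0/17 = 5.9 points (−13.2 to 27.0). With it missed, 0/17 − 0/17 = 0 points (−18.4 to 18.4).

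One missed event can therefore be the whole observed difference. These figures show the weight of an event, not its likelihood.

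**The case against.** The strongest reply is that death is already in the plan, and at a higher tier. It is a listed adverse event, not worded as exercise-related, and adverse events are a primary outcome. The second limb of primary outcome (v) refers to a subject without naming an arm, and a death does end participation. The 24-hour window governs withdrawal and does not define an adverse event. Much of this stands: the text does not say that control deaths are excluded, and a death would be seen in the adverse-event list or the subject flow. A reader might infer that deaths could vanish from the trial's safety evidence altogether, and the document does not support that. What remains is that the word acute and the two limbs do not clearly give an equal count by arm, and that outcome (iv) would still score the subject as not worsened.

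Two other stronger readings are tempting.

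- That lone PAH admissions and transplant listings are as large a gap as death. The rule does leave them out, but the other items are broad: any dose increase, peripheral oedema, one WHO class, a few days of worsening dyspnoea. Most such patients would be expected to have a second item. The article gives no rate either way.
- That the analysis rules would turn a death into a carried-forward good status. The imputation "method will be used to impute missing data at 12 and 24 weeks for the intention-to-treat analysis" concerns data missing at the scheduled assessments, while the withdrawal text calls worsening a time to event, for which no visit value need be carried forward. "Per protocol analysis will be restricted to the data from subjects who complete all assessments" is an ordinary restriction, and an intention-to-treat analysis is planned as well. Handling of event outcomes may be set out in a fuller plan that is not shown.

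It is also fair to say that this is the last of four secondary outcomes in 34 subjects, and that one event against none settles nothing: Fisher's two-sided p is 1.0. That limits the consequence but does not make the definition right. The list is cited to outside sources that cannot be checked here, but its use as an outcome is the plan's own choice.

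**Conclusion.** The point holds for death. Outcome (iv) is fixed by reference to a closed rule which, followed as written, scores a death without two documented items as no worsening and scores two test changes as worsening. Primary outcome (v) does not clearly make up for this with an equal between-arm count.

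The size is one event in 17, or 5.9 percentage points per missed death. This rests on 17 per arm being randomised and on an event occurring at all, for which the article gives no rate. The omission of lone PAH admissions and transplant listings is real but lesser. No conclusion is drawn about last observation carried forward, or about deaths going unreported. The change is worth making because the defect lies in a stated definition that bears on the safety hypothesis and is easily put right.

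**What to change.** Separate the outcome from the withdrawal rule. Leave the two-of-ten rule unchanged for withdrawal. For outcome (iv), write: death from any cause, or meeting the two-item rule, counted in both arms from randomisation to 24 weeks. Report deaths, PAH hospitalisations and transplant listings by arm as components. Letting a PAH hospitalisation or transplant listing count alone is a reasonable further step, but not essential.

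The cost is more than wording. Vital status and these events must be recorded to 24 weeks in subjects who withdraw, and the article describes no such follow-up. All subjects are patients of one service, so this should be practicable, and no new tests are needed. If admission alone qualifies, some admissions that do not reflect progression would count as worsening; reporting by component makes that visible.

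### Stopped exercise is an adverse event only in class, so home sessions stopped for a listed symptom without medical contact are left out of a primary safety outcome

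*Protocol article*

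**What the plan says.** The Withdrawal Criteria section of the protocol article gives the adverse events as a list of five kinds. Item (iv) is "an incident resulting in the patient ceasing exercise during class", followed by symptoms and signs that include chest pain, syncope, worsening dyspnoea and arrhythmia. No other item names a class; item (ii), for example, is any "exercise-related incident requiring presentation to the Emergency Department or General Practitioner".

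The supervised programme consists of "3 exercise classes (one hour duration) each week" for 12 weeks. The home programme is separate. Subjects are asked to "commence one session per week of their home exercise program during the last 4 weeks of their supervised program", and afterwards "subjects will increase the frequency of their home program to 3 sessions per week for an additional 12 weeks". The record described for home training is a log: "Subjects will be required to record each session on an exercise log".

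In the Outcomes section, primary outcome (v) is the number of acute adverse events reported during exercise training, and of those leading to withdrawal. It is not restricted to class. The Design/Methods part of the abstract puts the home programme inside the question of whether training is safe. The Discussion says that assessment after the home programme "will determine whether the subjects were able to safely maintain the benefits achieved during the supervised exercise training period".

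**The concern.** Item (iv) is the only one of the five that makes an exercise-provoked symptom an adverse event in itself, without a medical contact, an admission or a death. Limiting it to class means that the same incident is counted in the gymnasium and not counted at home. The definition is therefore narrower than the outcome it feeds and narrower than the safety conclusion that the abstract and Discussion intend to draw.

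Adverse events are a primary outcome, and the second hypothesis is that exercise training is safe. An under-count of milder home events works in favour of that hypothesis. A low home count could come from the definition alone, and the published result would not let a reader tell the difference.

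**Working it through.** **Which items can reach a home session**

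| Item | Tied to class? | Applies to a home session? |
|---|---|---|
| (i) medical emergency team call | No, but judged by the hospital's criteria | Unlikely |
| (ii) exercise-related emergency department or GP visit | No | Yes |
| (iii) admission for PAH or worsening right heart failure | No | Yes |
| (iv) exercise stopped for a listed symptom or sign | Yes | No |
| (v) death | No | Yes |

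The uncovered event is specific: a home session stopped for a listed symptom, with no event under (ii), (iii) or (v).

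**How much training lies outside item (iv)**

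The plan states no session total, so there is no figure to reproduce. The inputs come from the Exercise group and Home exercise program sections.

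- Supervised: 12 weeks × 3 = 36 sessions.
- Home, overlapping the supervised period: 4 weeks × 1 = 4.
- Home, after the supervised period: 12 weeks × 3 = 36.
- Home total: 4 + 36 = 40. All sessions: 36 + 40 = 76.
- Home share: 40/76 = 52.6%.

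If the weekly home session in the overlap replaced a class, the count would be 40 of 36 − 4 + 40 = 72, or 55.6%. The text reads more naturally as three classes plus one home session, so I use 40 of 76. Over the 17 planned exercise subjects with full adherence, this is 17 × 40 = 680 of 17 × 76 = 1,292 sessions.

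**From sessions to missed events**

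Let the rate of stop-events per session be the same in both settings, and let *m* be the proportion of home stop-events that are counted anyway through items (ii), (iii) or (v). Then

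share missed = 40 × (1 − *m*) / 76.

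At *m* = 0 this is 52.6%, and at *m* = 1 it is 0. The documents give no value for *m*, so 53% is an upper bound under these assumptions and not an estimate. Adherence that falls by the same factor *a* in both settings leaves it unchanged: 40*a*/(36*a* + 40*a*) = 52.6%.

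**The case against.** The strongest reply is that most of the safety net does extend to the home phase, and this largely stands. Items (ii), (iii) and (v) have no class limit. The withdrawal provision for serious adverse events refers to a training session and not to a class. The Statistical methods section treats the home programme as exercise training. Worsening clinical status is a secondary outcome, and its criteria include functional class, walk distance, right heart failure and progressive dyspnoea. A reader might infer that symptomatic events at home are never adverse events. The documents do not support that; only those without medical contact, admission or death fall outside. Clinical worsening does not close this gap, however, because it needs two or more criteria of deterioration and is not a count of acute exercise events.

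Second, the class limit has a practical reason. Some item (iv) signs, such as blood pressure changes, arrhythmia, or a heart rate abnormality measured by monitor and confirmed by palpation, cannot be detected reliably by a subject at home. This stands, and it shapes the fix. It does not explain leaving out chest pain, syncope or breathlessness, which subjects can report.

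Third, the log may already have a symptom field, since a condensed article need not describe its forms. That is fair, but an entry on the log would still not be an adverse event under item (iv) as written. The point concerns the stated definition, not missing detail.

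Fourth, the equal-rate assumption is unsupported. Home training omits cycling and upper limb work, and full adherence is unlikely in a plan that allows 20% attrition and accepts 75% class attendance. This is why 53% is not offered as an expected loss.

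**Conclusion.** The inconsistency is real and should be corrected, but it is limited. A home session stopped for a listed symptom, without a medical visit, relevant admission or death, is not an adverse event, while the same incident in class is. Primary outcome (v) and the home-safety aims in the abstract and Discussion are wider than that definition. The affected setting holds 40 of 76 prescribed sessions. The share of stop-events missed lies between 0 and 53% if rates per session are equal and adherence is full; if the home rate were higher than the class rate, the share could exceed 53%. The most serious events remain captured.

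Two further inferences are tempting and should not be drawn. A reader might suppose that the treating service would learn of such an event only at the 24-week assessment; the article does not describe contact during the home phase, and both groups receive usual medical care. A reader might also suppose that the trial will declare home training safer than class training; no comparison of the two phases is planned. What follows is only that a low home count could not be taken at face value.

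**What to change.** Reconcile the adverse-event list, primary outcome (v), the abstract and the Discussion:

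- For the purpose of outcome (v) only, let item (iv) cover any supervised or home training session.
- Record on the existing exercise log, for each session, whether it was stopped early and which self-detectable listed symptoms occurred, if the log does not already do so.
- Report outcome (v) separately for supervised and home sessions, with sessions as the denominator, and do not pool them. Observed and self-reported events are not ascertained alike.

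If the definition is to stay as it is, limit the safety conclusion for the home phase to events needing medical contact and to clinical worsening. In either case the withdrawal rule and clinical management stay unchanged.

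The cost is one clarified definition and at most one added field on a form subjects already complete. The downside is that home events would be self-reported and less precise than those seen in class, and the reported number of events may rise.
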